### Economic evaluation

A comprehensive cost-effectiveness analysis will be undertaken at the level of the OSHC service. To undertake this the resources used in developing and implementing the intervention will be meticulously quantified. Resources recorded will include the staff time, cost of materials and equipment, travel, and any training sessions. These costs will be assigned monetary values using established unit-cost data from reputable published sources (e.g. Australian Bureau of Statistics Wage Price Index),^32^ or market-rates. Prices will be updated to a common year prior to analysis to account for the effects of inflation.^32^ The total costs to provide the intervention will be calculated individually for all participating OSHC services. The primary outcome of the cost-effectiveness will be presented as an Incremental Cost-Effectiveness Ratio (ICER). The ICER will represent the incremental cost for each additional percentage point improvement in the number of OSHC services adhering to the physical activity and screen time guidelines at 12-month follow-up (i.e. the incremental cost of achieving better adherence in the intervention group versus the control group. Sensitivity analyses will be conducted to assess the robustness of our findings. Both one-way and multi-way sensitivity analyses will be employed to explore the effects of potential variations in key variables like resource utilization, the effectiveness of the intervention, and unit costs on the estimated ICER and therefore cost-effectiveness of the intervention.^33^

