Throughout 2019-20, we led a stakeholder consultation process to develop evidence-based physical activity and screen time guidelines for the Australian OSHC sector.^11^ The work was informed by a scoping review of OSHC-related physical activity and/or screen time guidelines around the world,^12^ a systematic review of OSHC-related physical activity intervention studies,^13^ and an international Delphi study which surveyed 67 stakeholders, including OSHC staff, families, government representatives, and child health experts.^11^ During the four-round Delphi process, we developed the first Australian OSHC physical activity and screen time guidelines; the first national scale OSHC guidelines anywhere in the world. The draft guidelines were provided to all Australian OSHC coordinators (*n* = 3518) for feedback, with 566 (16%) responding.^10^ The final guidelines (Fig. 1) use a 3:1 ratio for offered physical activity to physical activity achieved, based on the rationale that children are not physically active for the entire duration of playtime. Consequently, the guidelines recommend that OSHC services offer 45 minutes of active play before school, 90 minutes after school, and 180 minutes during vacation care sessions. These durations are designed to result in children achieving 15 minutes, 30 minutes, and 1 hour of physical activity, respectively. These recommendations align with the Australian physical activity guidelines, which suggest that children should accumulate at least 60 minutes of MVPA each day.^14^ By offering physical activity within OSHC, these guidelines help ensure that children have ample opportunities to meet their daily physical activity requirements. The guidelines have been endorsed by the national peak body, the Australian National Outside School Hours Services Alliance (NOSHSA).^15^

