## Discussion

This Type 2 hybrid effectiveness-implementation randomised controlled trial aims to implement and critically evaluate the Activated OSHC program’s impact on children’s physical activity and screen time in Australian OSHC services. By rigorously assessing the program’s effect on adherence to newly established physical activity and screen time guidelines, as well as analysing cost-effectiveness, acceptability, and feasibility, the study addresses a significant gap in current extended care practice. The trial’s findings will contribute to the growing body of evidence supporting structured interventions within the childcare sector, especially in out-of-school settings that are crucial for children’s daily activity patterns.

A key strength of this study lies in its hybrid trial design, which intertwines the evaluation of both the effectiveness of the Activated OSHC program and the processes underlying its implementation. This dual focus is complemented by the use of validated observational tools and robust data analysis methods, enabling high reliability and validity of the results. The trial’s design also ensures diverse representation of OSHC services in metropolitan and regional locations across 3 Australian states and, by including a stratified sample based on socioeconomic status, enhances the generalisability of the findings. Additionally, the use of a multidisciplinary approach, incorporating perspectives from stakeholders across the health and education sectors, further underscores the robustness and relevance of the research.

The implications of this study are multifaceted. At its core, the Activated OSHC program is designed to be a sustainable program to enhance current extended care practices. It dovetails with established policy-based accreditation systems (such as SunSmart), providing a dual benefit: promoting healthier behaviours in children and offering OSHC services a mark of distinction through accreditation. Such a credential can serve as a mark of quality, potentially aiding services in positioning themselves favourably in a competitive market.

As we contemplate scaling the program nationally, insights from this trial will be crucial for understanding the nuances of large-scale implementation. The promise of the Activated OSHC program extends to its potential influence on policy, particularly if the findings confirm that the guidelines are effective and sustainable when implemented broadly.

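### One-off development cost is merged with delivery cost in a single ICER, so the result depends partly on trial size and does not carry over directly to a national roll-out

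*Protocol article*

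**What the plan says.** The Economic evaluation section sets out the cost side in three steps. To carry out the analysis, "the resources used in developing and implementing the intervention will be meticulously quantified". The items are then listed: "Resources recorded will include the staff time, cost of materials and equipment, travel, and any training sessions". Finally, "The total costs to provide the intervention will be calculated individually for all participating OSHC services".

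The ICER is the "incremental cost for each additional percentage point improvement in the number of OSHC services adhering to the physical activity and screen time guidelines" at 12 months, explained as "the incremental cost of achieving better adherence in the intervention group versus the control group". One-way and multi-way sensitivity analyses are to examine the effect of "potential variations in key variables like resource utilization, the effectiveness of the intervention, and unit costs on the estimated ICER".

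The section does not split development from delivery, does not state how development is shared out between services, and names no ICER without it. On intended use, the Discussion says: "As we contemplate scaling the program nationally, insights from this trial will be crucial". The Introduction makes cost-effectiveness one of the five research questions and asks for solutions that are cheap and can be scaled.

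**The concern.** The program was built once: co-design workshops, a manual, four online modules and family resources (Intervention section). That spending does not grow when another service joins. Manuals sent out, posters, signage, support and staff training time do grow.

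An ICER that adds the two answers a mixed question. Part of it is what a service costs to bring in; the rest is what was spent beforehand, divided by however many services the trial happened to allocate to the program. A decision-maker considering a national roll-out needs the first part. If only the sum is published, the first part cannot be recovered, and the program may look dearer to extend than it is.

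**Working it through.** The plan states no cost, ICER or willingness-to-pay figure, so there is no economic result to reproduce. The check is algebraic, followed by an illustration.

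**Inputs from the Protocol article**
- Intervention services: 96 (Abstract, Methods).
- Planned effect: 61% − 41% = 20 percentage points (Sample size and statistical analysis).
- National count: 3518. The Introduction says "The draft guidelines were provided to all Australian OSHC coordinators" and gives this number. It serves here as a proxy for services.

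**Assumed, because the documents give no costs**
- D, one-off development cost: $50,000 to $300,000.
- v, delivery cost per service: $500 or $1,500.
- Development is shared equally over the intervention services.

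**Formulas, per service per percentage point**
- Trial ICER with development: (D/96 + v)/20
- ICER without development: v/20
- Development spread nationally: (D/3518 + v)/20

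**Development share, needing no dollar figure**
- Trial: D/(96 × 20) = D/1,920.
- National: D/(3518 × 20) = D/70,360.
- Ratio: 3518/96 = 36.6. With N adopting services it is N/96; if half of 3518 adopted, 1759/96 = 18.3.
- Trial size alone moves it. The plan has 81 metropolitan services per arm and adds 15 regional ones. Going from 81 to 96 lowers the development share by 1 − 81/96 = 15.6%, with no change in the program.

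**Illustration**

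| D | v | Trial ICER, with development | Part due to development | Without development | Spread over 3518 |
|---|---|---|---|---|---|
| $50,000 | $500 | $51.04 | 51% | $25.00 | $25.71 |
| $100,000 | $500 | $77.08 | 68% | $25.00 | $26.42 |
| $300,000 | $500 | $181.25 | 86% | $25.00 | $29.26 |
| $50,000 | $1,500 | $101.04 | 26% | $75.00 | $75.71 |
| $100,000 | $1,500 | $127.08 | 41% | $75.00 | $76.42 |
| $300,000 | $1,500 | $231.25 | 68% | $75.00 | $79.26 |

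For example, with D = $100,000 and v = $500: 100,000/96 = 1,041.67; (1,041.67 + 500)/20 = 77.08; and 1,041.67/1,541.67 = 68%.

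If the numerator is the total for the arm rather than the mean per service, it is D + 96v. The part due to development, D/(D + 96v), is the same.

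**The case against.** The case for leaving the section alone is a fair one.

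- **Choice of perspective.** A trial-based ICER may include development cost. This stands: inclusion is not an error.
- **Apportionment is not stated.** The text says development is quantified, not that it is divided by 96, and the per-service figure is described as the cost of providing the program. This stands in part. Because development is quantified expressly for this analysis and only one ICER is defined, the natural reading is that it enters that ICER. The division by 96 is nevertheless an assumption of this check.
- **Sensitivity analyses.** The listed variables are examples, so dropping a cost component could be fitted in. That is possible, but neither an ICER without development nor a different number of sharing services is named.
- **Stated use.** The Discussion speaks of insights for scaling and does not name the ICER as the roll-out figure. This stands, although the ICER is the only economic summary measure defined.
- **Size.** The dollar figures are assumed, and 3518 implies adoption by every service. This also stands, and is why the ratio is given as N/96.

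A reader might also infer that control-arm costs are left out and that the numerator is therefore gross rather than incremental. The documents do not support this. The ICER is defined as intervention versus control, costs are computed for all participating services, and the Abstract lists cost among the coordinator survey topics without limiting it to one arm. Only resources for the program are counted, and controls have no access to it until after the 12-month assessment (Allocation and blinding). Program cost therefore equals incremental cost unless the program changes usual-practice spending. If it changes such spending by u per service, the ICER moves by u/20, or $25 for each $500. The size and sign of u are unknown, and it is zero if usual-practice costs do not differ between arms. How control services are costed in detail is what an article leaves to the full plan.

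**Conclusion.** The point holds for development cost only. As written, one-off and recurring costs go into one ICER, and the section promises no result that separates them. The development share per service is 36.6 times larger over 96 services than over 3518. That factor applies to this share alone. The effect on the whole ICER depends on D and v, which the documents do not give; over the assumed ranges, development makes up 26% to 86% of the trial figure.

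It would be too strong to say that the ICER is not incremental or is of no use for scale-up. It is a valid trial-based figure that cannot be carried directly to a roll-out without the split. The effectiveness analyses are untouched. The conclusion assumes that development enters the published ICER, that it is shared equally over the intervention services, and that it need not be repeated for later adopters.

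**What to change.** In the Economic evaluation section:

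1. Record development and delivery as separate cost lines, and say which resources belong to each.
2. Report the ICER both with and without development cost, stating how development is shared out.
3. Add one scenario that spreads development over an expected number of adopting services, giving that number and its basis.
4. State that research-assessment costs are excluded. Travel is on the resource list without saying whether it is for the program or for the observation visits.

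The cost is one or two more ICER lines, drawn from resources that are being itemised anyway. No new data collection is needed for the split, provided the two categories are kept apart as costs are logged.

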## Discussion

This Type 2 hybrid effectiveness-implementation randomised controlled trial aims to implement and critically evaluate the Activated OSHC program’s impact on children’s physical activity and screen time in Australian OSHC services. By rigorously assessing the program’s effect on adherence to newly established physical activity and screen time guidelines, as well as analysing cost-effectiveness, acceptability, and feasibility, the study addresses a significant gap in current extended care practice. The trial’s findings will contribute to the growing body of evidence supporting structured interventions within the childcare sector, especially in out-of-school settings that are crucial for children’s daily activity patterns.

A key strength of this study lies in its hybrid trial design, which intertwines the evaluation of both the effectiveness of the Activated OSHC program and the processes underlying its implementation. This dual focus is complemented by the use of validated observational tools and robust data analysis methods, enabling high reliability and validity of the results. The trial’s design also ensures diverse representation of OSHC services in metropolitan and regional locations across 3 Australian states and, by including a stratified sample based on socioeconomic status, enhances the generalisability of the findings. Additionally, the use of a multidisciplinary approach, incorporating perspectives from stakeholders across the health and education sectors, further underscores the robustness and relevance of the research.

The implications of this study are multifaceted. At its core, the Activated OSHC program is designed to be a sustainable program to enhance current extended care practices. It dovetails with established policy-based accreditation systems (such as SunSmart), providing a dual benefit: promoting healthier behaviours in children and offering OSHC services a mark of distinction through accreditation. Such a credential can serve as a mark of quality, potentially aiding services in positioning themselves favourably in a competitive market.

As we contemplate scaling the program nationally, insights from this trial will be crucial for understanding the nuances of large-scale implementation. The promise of the Activated OSHC program extends to its potential influence on policy, particularly if the findings confirm that the guidelines are effective and sustainable when implemented broadly.

Finally, the national scale of this Australian OSHC physical activity and screen time guidelines and this trial may provide a compelling model for the international community. This could inspire similar initiatives worldwide, showing that strategically designed, policy-aligned interventions can become integral to enhancing the developmental environments of children across diverse settings.
